##### Trauma film paradigm

The trauma film paradigm is used in this study to elicit intrusive memories [17]. Clips from two films are viewed in a small, sound attenuated room, and presented on a 24-inch screen with over-ear headphones for audio. Participants first complete a questionnaire about their current emotional state. They watch the trauma film (~12 min in total), which includes two scenes, one from the film Irréversible [57] and the other from a UK public safety advertisement on the dangers of texting and driving [58]. Both film scenes are fictional and have been used in previous studies [56, 59–63]. Film order is counter-balanced. Whilst participants view the films, we ask they maintain their concentration and continuously look at the scene. Upon completion, they rate their current level of distress and degree to which they were able to pay attention to the films. A camera in the room is used to monitor participants’ attention to the film. Participants are told prior to participating in the study they may watch positive, neutral or negative scenes, and are informed about the contents of the negative scenes prior to watching.

#### Recognition and mind wandering tasks

Following the 2-h sleep or wake opportunity, participants complete two tasks. The first is a recognition task. Participants view targets (images from the films) and lures (similar images never seen) and are required to judge whether they witnessed these during the film. The task includes 64 images in total and takes ~10–15 min to complete. Recognition memory task performance will be assessed with the discriminability index (*d-prime* = transformed hits rate − transformed false alarm rate). As a planned secondary analysis, performance on targets, and lures will be individually examined as findings in the literature are inconsistent as to whether performance on targets or lures is driving sleep-related effects on *d-prime* [13, 40].

Mind wandering or off-task thought is related to failures of attention on a range of different sustained attention tasks [64]. The mind wandering task in the current study is an adapted version of a sustained attention to response Go/NoGo task, which has previously been used to elicit and examine mind wandering [65]. Participants are instructed to pay attention to a series of digits and press a button for all digits except the digit 3. The presentation of stimuli is stopped at random times (every 30–70 s) to probe mental state (eg, on/off task) and vigilance of the participants with a series of questions, taking ~18–20 min to complete. The primary outcome from the mind wandering task is frequency of mind wandering.

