### Aims and hypotheses

The overall objective of this project is to examine two mechanisms underlying the relationship between sleep and the development of involuntary intrusive memories, utilizing a well-established experimental analog trauma exposure. The two mechanisms are:

Improved memory consolidation over periods of sleep leads to integration of the trauma memory into the broader memory network, thereby reducing intrusive memories.Sufficient sleep quality/quantity facilitates executive control over spontaneous cognition, including intrusive memories, decreasing the likelihood of their occurrence.

This study will employ a between-subjects design, with two conditions: (1) 2-h daytime nap opportunity, measured using polysomnography; and (2) equal length of controlled waking. Each condition will include *n* = 57 healthy adults, aged 18–49 years old (total *N* = 114, aiming for equal numbers of women and men). OSF preregistration: https://doi.org/10.17605/OSF.IO/MWAHD

Aim 1: Examine the effect of a daytime nap (vs. wake) on intrusive memory frequency.
Hypothesis 1.We will replicate the established finding that a nap, relative to wake, will result in a reduced number of intrusive memories [14, 15] in the 5 days following viewing the trauma film.

Aim 2: Investigate the effect of sleep-related memory consolidation on intrusive memory frequency.
Hypothesis 2a.A nap, relative to wake, will lead to greater recognition memory for the trauma film stimuli immediately after the nap/wake period, as measured by improved recognition of trauma stimuli from the film and reduced endorsement of lure stimuli (film images never seen).
 Hypothesis 2b.Recognition memory for the trauma film immediately after the nap/wake period will mediate the relationship between sleep condition (nap vs wake) and the number of intrusive memories in the following 5 days.

Aim 3: Investigate the effect of overnight sleep on mind wandering and intrusive memory frequency over a 5-day period following analog trauma exposure.
Hypothesis 3a.Reduced quantity of sleep at night will be associated with increased mind wandering and greater frequency of intrusive memories the next day.
 Hypothesis 3b.Mind wandering will mediate the relationship between sleep the previous night and intrusive memories the following day.

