### Participants and recruitment

#### Sample size

Our target sample size is 114 participants, with 57 in each condition. This study is powered primarily on Hypothesis 1, the group effect (nap vs. wake) on intrusive memory frequency. Relevant effect sizes were derived from a variety of prior studies, which have also been reported within at least one of four meta-analyses. Previous studies [14, 15, 25] examining the effect of a nap compared to wake on intrusion frequency have detected small to medium effect sizes (Hedges’ *g* = 0.38 [26] and 0.69 [15]) for between-group differences in intrusive memory frequency in the days following the experimental manipulation. Gvozdanovic et al. (2023) [14] also found a nap led to significantly fewer intrusive memories than the wake group, however, an effect size was not provided. For studies examining recognition memory for the trauma film following overnight sleep compared to wake or partial sleep deprivation [13, 23, 40], we calculated a sample size weighted average for Cohen’s *d*, finding a medium effect size of 0.5 for between-group differences where sleep, relative to wake, led to improved recognition memory for the film. Consistent with these studies, to detect a medium effect size of 0.5, with a two-tailed α of 0.05 and 80 per cent power, 57 participants are needed per group (114 participants in total) [41].

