## Analytic strategies

All analyses will be conducted in R.

Aim 1: The effect of a daytime nap (vs wake) on total intrusive memory frequency will be analyzed with a generalized linear mixed-effects model. Sex and day will be included as covariates. A random intercept for participant will be included to account for repeated measures across days.

Aim 2: The effect of sleep-related memory consolidation on intrusive memory frequency will be analyzed with regression and mediation analysis. Specifically, Hypothesis 2a (a nap will lead to greater recognition memory for the trauma film) will be examined with multiple regression, whereby recognition memory immediately after the nap/wake will be predicted by Condition. For Hypothesis 2b (recognition memory will mediate the relationship between sleep and intrusive memories), we will utilize mediation analysis, with Condition as the explanatory variable, recognition memory immediately after the nap/wake as the mediator, and total number of reported intrusive memories as the dependent variable. A Monte Carlo power analysis was conducted for the mediation model. A sample size of *n* = 114 has limited power to detect the indirect effect. Nonetheless, given the strong theoretical rationale for the mediation analysis and the value for future research in determining effect sizes, we will conduct the analysis and consider Hypothesis 2b as a secondary analysis. We will report effect sizes and confidence intervals of each path. We will also conduct parallel exploratory analyses for both Hypotheses 2a and 2b, utilizing recognition memory on day 5, rather than memory immediately following the nap/wake. This will explore the role of longer-delay memory consolidation on intrusive memory. Note, Hypothesis 2b may appear dependent on the success of Aim 1.

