We will exclude data from the recognition memory task if the participant is not a conscientious responder. This is operationalized as below 50 per cent performance for both targets (images they have seen) and lures (images they have not seen).

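### Examining targets and lures separately cannot show which one drives the nap effect on d-prime; that asymmetry is the Condition effect on the criterion c, which the article does not test

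*Protocol article*

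**What the plan says.** Under Recognition and mind wandering tasks, the article states: "Recognition memory task performance will be assessed with the discriminability index", defined as "transformed hits rate − transformed false alarm rate". On the task itself it says "The task includes 64 images in total"; the split between targets and lures is not given. The secondary analysis follows: "performance on targets, and lures will be individually examined as findings in the literature are inconsistent as to whether performance on targets or lures" are what produces the sleep effect on d-prime. Its stated purpose is thus attribution, not only description.

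Hypothesis 2a, under Aims and hypotheses, is worded through the same two components: "as measured by improved recognition of trauma stimuli from the film and reduced endorsement of lure stimuli". Under Analytic strategies the model for it is a regression in which "recognition memory immediately after the nap/wake will be predicted by Condition". Under Data exclusion, a participant is dropped from this task only when performance is below half on both image types, so someone who answers yes (or no) to nearly every image stays in. The article names no criterion or response-bias measure as an outcome, covariate or check.

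**The concern.** A hit rate and a false-alarm rate each mix two things: how well a person separates old images from new ones (d'), and how readily that person says yes (the criterion c). Better sensitivity raises hits and lowers false alarms by the same amount on the z scale. What makes one move more than the other is c. Two separate examinations of targets and lures therefore do not test the quantity that the driver question asks about.

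At stake is the reading of one secondary analysis. The article motivates it by disagreement in earlier studies over targets and lures. Two separate results could reproduce such disagreement by chance alone, or through a difference in willingness to say yes.

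**Working it through.** **Inputs from the article.** d' = z(hits) − z(false alarms); 57 per arm; standardised effect 0.5; two-sided 0.05; 64 images.

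**Assumed, because the article does not give them.** Wake-arm d' of 1.5 (1.0 and 2.0 also tried); the between-person SDs of d' and c stated in each step; 32 targets and 32 lures where images are simulated.

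**The article's own figure.** The Sample size section says "to detect a medium effect size of 0.5, with a two-tailed α of 0.05 and 80 per cent power, 57 participants are needed per group". Those inputs give 63 per group by the normal formula and 64 by the t test; 57 per group gives about 75% power (t test). That is a separate matter. Here 57 is only the number analysed.

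**1. Identity.** With c = −[z(H) + z(F)]/2:
- z(H) = d'/2 − c and z(F) = −d'/2 − c.
- Target gain = Δz(H) = Δd'/2 − Δc.
- Lure gain = −Δz(F) = Δd'/2 + Δc.
- Lure gain − target gain = 2Δc.

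For a fixed Δd', the split depends on Δc alone, whatever the simulation settings.

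**2. One sensitivity gain, three appearances.** Wake arm: d' = 1.5, c = 0, so H = Φ(0.75) = 77% and F = Φ(−0.75) = 23%. The nap arm has d' = 2.0 throughout:

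| c in nap arm | Hits | False alarms | Appears as |
|---|---|---|---|
| 0 | Φ(1.00) = 84% | Φ(−1.00) = 16% | both |
| +0.25 | Φ(0.75) = 77% | Φ(−1.25) = 11% | lures only |
| −0.25 | Φ(1.25) = 89% | Φ(−0.75) = 23% | targets only |

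**3. Two separate tests when the gains are truly equal.** SD of d' = 1, Δd' = 0.5, Δc = 0, 57 per arm. Each component gains 0.25, and its SD is √(0.25 + SD_c²).
- SD_c = 0.3: SD 0.583, standardised effect 0.25/0.583 = 0.43, power 62% per test. The two components correlate at (0.25 − 0.09)/(0.25 + 0.09) = 0.47. By simulation, exactly one test is significant in 33% of trials.
- SD_c = 0.5: SD 0.707, standardised effect 0.25/0.707 = 0.35, power 46% per test, correlation 0. Exactly one is significant in 2 × 0.46 × 0.54 = 50%.

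A direct test of c rejects in about 5% of trials, as it should when Δc = 0.

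**4. With binomial responses to 32 targets and 32 lures.** SD of d' = 0.6, SD of c = 0.3, Δd' = 0.35 (standardised effect about 0.5), 4,000 runs:

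| Δc | d' significant | c significant | Targets only | Lures only | Both |
|---|---|---|---|---|---|
| −0.175 | 73% | 74% | 90% | 0.3% | 5% |
| 0 | 74% | 5% | 25% | 25% | 20% |
| +0.175 | 73% | 73% | 0.4% | 91% | 5% |

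A wake-arm d' of 1.0 or 2.0 gives the same pattern. With no sensitivity gain and Δc = ±0.175, each separate test is significant in about 45% to 47% of runs, while d' rejects in 5%.

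**The case against.** **No decision rule is written.** The article says the two will be examined individually. It sets no threshold and does not say that one significant and one non-significant result identifies the driver; estimates with intervals would fit the wording equally well. This stands, so the third-to-a-half figure is conditional on such a reading. The identity is not: no pair of separate examinations compares the two gains directly.

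**The main test is protected.** A reader might infer that a more cautious nap group could be mistaken for a consolidation effect under Hypothesis 2a. The documents do not support that. Recognition performance is assessed by d-prime, which a pure criterion shift leaves unchanged. Pure caution would also lower hits: at d' = 1.5, moving c from 0 to +0.25 takes hits from 77% to 69% and false alarms from 23% to 16%. That contradicts the half of Hypothesis 2a that expects better recognition of film images.

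**c does not identify a cause.** Yes/no data cannot separate a moved criterion from a change in target or lure strength; sleep could truly alter lure familiarity, and this would appear as a shift in c. This stands. A shift in c therefore cannot license a memory-based statement that targets or lures drive the effect.

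**Little information is lost.** d' and c are a one-to-one re-expression of z(hits) and z(false alarms), and a fuller plan may already include c. This is true, and it is why the change is small. But the attribution question is posed in this article, and the analysis named beside it does not answer it.

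**Conclusion.** The point holds as a low-cost improvement to one secondary analysis. Under the equal-variance model behind d-prime, the target/lure asymmetry is exactly the Condition effect on c, and the article plans no test of that effect. If the driver were read from two separate tests, equal true gains would leave exactly one significant in roughly a third to a half of trials. That range assumes 57 per arm, a d' effect of 0.5 SD and an SD of c between 0.3 and 0.5; the SD of c and the 32/32 image split are assumptions. The Hypothesis 2a test and the Hypothesis 2b mediator, taken as d-prime, are unaffected, and so is Hypothesis 1.

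**What to change.** Keep d-prime as the sole test of Hypothesis 2a. Recast the secondary analysis as follows:
- Report the Condition effect on c = −[z(hits) + z(false alarms)]/2 with its confidence interval, beside d'. A probit mixed model on the 64 responses with Condition, image type and their interaction is equivalent.
- Give hit and false-alarm rates by arm with intervals, as description. This keeps the results comparable with earlier studies.
- Say that the effect lies mainly in targets or mainly in lures only if the effect on c supports an asymmetry.
- State that a shift in c may reflect response bias or a change in target or lure strength, which yes/no data cannot separate.

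The cost is one derived score from responses already collected, a few lines of text, and a more cautious statement about targets and lures. Under Data sharing and dissemination, final analysis starts only after data collection ends, so the change can still be made in advance.

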##### Intrusive memory diary (days 0–5)

Following completion of the cognitive tasks, participants are provided with a definition of intrusive memories and instructions for completing the intrusive memory diary. The diary is completed online, accessible via smartphone, or computer. There are a total of seven questions, including the date and time of the intrusion, the type (eg, image, sound, thought(s)), content of the intrusive memory, whether the intrusive memory was triggered, and level of distress and vividness rating. This diary was based on an online diary used in a trauma film study by Zeng et al. (2021) [13].

An email with the intrusive memory diary link is sent to participants as soon as they leave the lab on day 0. Participants are instructed to complete the diary as soon as possible following the experience of an intrusive memory, completing this as many times as needed. A reminder with the intrusive memory diary link is also sent via text message to participants each evening (between 1 and 3 h prior to scheduled bedtime, based on the previous week), beginning the first evening following the lab session. Participants are instructed to fill out the diary at the end of the evening after receiving the text reminder, even if they have not experienced an intrusive memory. Participants can select an N/A option to each of the diary questions, reducing demand characteristics to report an intrusive memory even if one did not occur. Thus, participants complete the diary a minimum of six times. The primary outcomes from the intrusive memory diary are the total number of intrusive memories following the lab session and number of intrusive memories each day. Secondary outcomes include examining level of distress ratings (1 = not at all distressed, 9 = extremely distressed) when intrusive memories occur.

##### Post-lab session sleep monitoring (days 0–5)

Sleep (at-home) for five nights following viewing the trauma film is measured via actigraphy and sleep diaries. The night following the lab session, participants are required to follow their assigned sleep schedule. Across the remaining four nights participants are not required to follow a regular sleep schedule on these nights. Primary sleep variables measured during this time will be objective total sleep time and sleep efficiency. Secondary variables will include sleep diary-based variables (subjective total sleep time and sleep efficiency).

##### Post-lab session tasks (days 1–5)

For the 5 days following the lab session, participants complete daily intrusive memory diaries and daily mind-wandering task. Participants are instructed to complete the mind wandering task between the hours of 14:00 and 17:00 each day in a quiet environment. Participants are reminded via text and email each day at 13:55 to complete this task. They are required to complete this task on a computer or laptop with a hard keyboard. The recognition task is repeated once on day 5, with an instruction to complete this in a dark room or after sunset to ensure they can clearly view the images. Participants are instructed to complete the recognition task on a computer screen (rather than a smartphone) and are reminded via text and email on day 5. The links to the recognition task on day 5 and the mind wandering task each day are included in the reminder email. Figure 2 details the schedule of enrolment, study questionnaires, and tasks.

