### Data exclusion

All participants who complete the study will be included in the analysis, except as specified below. Data will not be imputed for the primary outcomes in this study. We will use sufficiently robust statistical models that accommodate missing data. Prior to the lab testing session (day 0), participants will be excluded if they have not adhered to at least five nights of the assigned sleep schedule and/or not adhered to the assigned sleep schedule for the two nights prior to the testing session. Participants are excluded from the study if they wake 30 min after their scheduled wake time on day 0. Participants are also excluded from the study if they do not follow the sleep schedule (or nap) following the lab session on day 0. For questionnaires assessing spontaneous cognition completed during PSG set-up on day 0, we may impute data for any missing responses using multiple imputation.

For the mind wandering task, for any given aim, participants will be included if they provide at least 1 day’s worth of data for that aim. We will exclude data where the participant has not understood the task or is not a conscientious responder (operationalized as below 50 per cent performance on both Go and NoGo trials). Participant understanding of the task will also be checked during a debrief at the end of the study. Timing of the mind wandering task is checked against sleep diary data, participant phone calls (regarding sleep and wake timing) and actigraphy data. If the task is completed more than 12 h post-wake time, data for that day will be excluded.

If participants report that they did not pay sufficient attention to the most graphic sections of either film and they are not observed to be watching the screen at least 80 per cent of the time, their data for the whole duration of the study will be excluded. For the intrusive memory diary, data will not be imputed. Only intrusive memories of the films are included. Unclear diary entries are discussed with participants during the debrief meeting at the end of the study. If the participant does not complete the intrusive memory diary for the entire duration of the study, their data will be excluded. We will not exclude participants who report a high number of intrusions, instead winzorization will be performed for outliers.

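### The day 5 recognition task shows film images again while the intrusion diary is still open, so the day 5 count and the total can include intrusions that the task cued

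*Protocol article*

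**What the plan says.** All places are in the protocol article.

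- **Task.** Under Recognition and mind wandering tasks, the recognition task has 64 images, made up of stills from the films and similar images that were never shown.
- **Repeat.** Post-lab session tasks (days 1–5): "The recognition task is repeated once on day 5, with an instruction to complete this in a dark room or after sunset". On delivery: "The links to the recognition task on day 5 and the mind wandering task each day are included in the reminder email". The only clock time for a task reminder is given for the mind wandering task: "Participants are reminded via text and email each day at 13:55 to complete this task".
- **Diary.** Under Intrusive memory diary (days 0–5), participants log intrusions as they occur and make an entry every evening. The text reminder goes out 1 to 3 h before scheduled bedtime: "Participants are instructed to fill out the diary at the end of the evening after receiving the text reminder". The section adds: "Thus, participants complete the diary a minimum of six times".
- **Outcome.** Same section, naming the total and the daily count: "The primary outcomes from the intrusive memory diary are the total number of intrusive memories following the lab session and number of intrusive memories each" […]. Hypothesis 1 covers the 5 days after the film.
- **What counts.** Data exclusion: "Only intrusive memories of the films are included". The diary also asks whether the intrusion was triggered, but no stated rule uses the answer.

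**The concern.** A repeat showing of film stills is a plausible cue for film memories. If it takes place before the diary closes, any intrusion it provokes meets the only content rule and enters the primary count as if it had arisen spontaneously.

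Day 5 contributes to Hypothesis 1, to the total used in Hypothesis 2b, and to one of the five day-level observations per participant in Aim 3. If spontaneous intrusions decline over the week, even a few cued events would be a sizeable share of that day. The exploratory mediation that uses day 5 recognition has a further difficulty: measuring the mediator may itself generate outcome events.

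**Working it through.** **1. Is day 5 evening inside the count?** Evening entries on days 0, 1, 2, 3, 4 and 5 make six, which reproduces the stated minimum. The day 5 evening entry is therefore counted.

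**2. Which comes first on day 5?** Eligible bedtimes run from 22:00 to 01:00. A text 1 to 3 h earlier arrives between 22:00 − 3 h = 19:00 and 01:00 − 1 h = 24:00, and the entry is due after that. A task done in a dark room in the afternoon, or soon after sunset, precedes the entry. A task done late in the evening may follow it. Task first is the likely order, but the text does not fix it. Earlier completion lengthens the exposed period.

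**3. Does any rule remove later intrusions?** None in the text. Data exclusion restricts by content (the films), not by time relative to the task or by the trigger item. The lab-session recognition task also shows film images, but it ends before the diary opens and is not part of this point.

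**4. Illustrative size.** No input below comes from the documents; all are assumptions.

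- T = wake-arm mean of uncued intrusions over days 1–5: 3 or 5
- True nap/wake ratio: 0.60
- c = cued intrusions per person, equal in both arms: 0.25, 0.5 or 1.0
- Observed ratio = (0.60·T + c) / (T + c)

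| T | c = 0.25 | c = 0.5 | c = 1.0 |
|---|---|---|---|
| 3 | 2.05/3.25 = 0.631 | 2.30/3.50 = 0.657 | 2.80/4.00 = 0.700 |
| 5 | 3.25/5.25 = 0.619 | 3.50/5.50 = 0.636 | 4.00/6.00 = 0.667 |

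On the log scale the loss is 1 − ln(0.619)/ln(0.60) = 6% at the low end and 1 − ln(0.700)/ln(0.60) = 30% at the high end.

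**5. Day 5 alone.** Assume daily rates decline as 1 : 0.6 : 0.4 : 0.3 : 0.2. Day 5 then holds 0.2/2.5 = 8% of T, or 0.24 to 0.40 uncued intrusions in the wake arm.

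- Low end (T = 5, c = 0.25): ratio (0.24 + 0.25)/(0.40 + 0.25) = 0.75; cued share in the wake arm 0.25/0.65 = 38%.
- High end (T = 3, c = 1.0): ratio (0.144 + 1)/(0.24 + 1) = 0.92; cued share 1/1.24 = 81%.

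**6. Does the day covariate deal with it?** Only in part. It can absorb an average day 5 shift. Under a log link (assumed, since none is stated) it scales both arms by the same factor, whereas equal additive cueing pulls the day 5 ratio toward 1. The total used in Hypothesis 2b has no day term.

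**The case against.** The strongest reply has four parts.

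- **The order may be fixed elsewhere.** Figures 1 and 2 are not shown, and the preregistration is not at hand. This stands as a caveat. The instructions that are visible do, however, allow the overlap.
- **Cueing is not demonstrated.** No passage shows that the images provoke intrusions, or how many. This stands, so the point is that the count can include such events, not that it does.
- **The dilution depends on cueing being additive and equal.** If cued events scale with each arm's own rate, the ratio stays at 0.60·T(1+k) / [T(1+k)] = 0.60. The Introduction links poor sleep to weaker control over traumatic memories, so a cued intrusion could still depend on sleep. The total also includes day 0, which enlarges the denominator and shrinks the dilution. All of this stands and limits the illustration.
- **The exposure is small and shared.** It is part of one of six diary days, and both arms do the same task. This also stands.

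A reader might go further and infer that the task biases the trial toward a nap effect, or that day 5 consists mostly of cued events. The documents support neither. Equal additive cueing moves the ratio toward 1. Cueing could differ by arm if the nap alters the response to the images, for instance through the better recognition predicted in Hypothesis 2a, but nothing shows that it does or in which direction. As for day 5, the cued share is only 38% at the low end of the assumptions. Nor is the task confined to the evening, since a dark room at any hour is allowed.

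**Conclusion.** The point holds as a limited design weakness. Film images are shown again inside the primary counting window, and the visible text neither orders the task after the final diary entry nor excludes later film intrusions. Following the plan as written can therefore count events that the study itself prompted.

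If cueing is similar and additive across arms, the result is a diluted nap/wake ratio and a noisier day 5 observation in Aim 3. It is not a spurious nap effect. The size is unknown. The range of 0.62 to 0.70 for a true 0.60 over days 1–5 rests wholly on the assumed rates, and its upper end needs one cued intrusion per person, about four times the assumed uncued day 5 rate of 0.24. This is a cheap improvement and not a threat to the validity of the randomised comparison.

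**What to change.** **Remaining participants.** Make the recognition task the last procedure on day 5. Release its link only once the final diary entry has been submitted, and end the intrusion count at that entry. An end-of-evening task remains compatible with the dark-room-or-after-sunset instruction.

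**Participants already tested.** Before final analysis, prespecify one of two sensitivity analyses:

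- omit day 5; or
- count only intrusions timed before the task started, with an offset for the shortened day 5 window. The diary records date and time and the task runs in Qualtrics, but no passage says that task start times are stored, so this must be checked first.

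The cut-off at task start should not replace the primary count for these participants. Task time was chosen by the participant after randomisation. It gives unequal day 5 windows, and a mid-afternoon task would discard most of the evening.

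**Cost.** One changed link order and one counting rule. A short part of the day 5 evening goes uncounted, and the instruction changes partway through recruitment, which is expected to run to July 2026. Allocation in equal-numbered blocks of six should keep the arms close to balanced on either side of the change; its date should be recorded.
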